# Cross-sectional experimental assessment of pain modulation as part of multidimensional profiling of people with cervicogenic headache: protocol for a feasibility study

**DOI:** 10.1136/bmjopen-2023-074743

**Published:** 2024-06-18

**Keywords:** feasibility studies, chronic pain, neurological pain, risk factors

## Abstract

**Background:**

An endogenous pain modulation profile, reflecting antinociceptive and pronociceptive mechanisms, may help to direct management by targeting the involved pain mechanism. For individuals with cervicogenic headache (CeH), the characteristics of such profiles were never investigated. However, the individual nature of experiencing pain demands profiling within a multidimensional framework including psychosocial lifestyle characteristics. The objective of the current protocol is to assess the pain modulation profile, which includes psychosocial lifestyle characteristics among people with CeH.

**Methods and analysis:**

A protocol is described to map pain modulation profiles in people with CeH. A cross-sectional non-randomised experimental design will be used to assess feasibility of mapping these profiles. The pain modulation profile is composed based on results on the Depression, Anxiety, Stress Scale, Pittsburgh Sleep Quality Index, Headache Impact Test and on responses to temporal summation of pain (pinprick), conditioned pain modulation and widespread hyperalgesia (mechanical pressure pain threshold and cuff algometry). Primary analyses will report results relating to outcomes on feasibility. Secondary analyses will involve an analysis of proportions (%) of the different psychosocial lifestyle profiles and pain profiles.

**Ethics and dissemination:**

Ethical approval was granted by the Ethics Committee Research UZ/KU Leuven (Registration number B3222024001434) on 30 May 2024. Results will be published in peer-reviewed journals, at scientific conferences and, through press releases. Protocol V.3. protocol date: 3 June 2024.

STRENGTHS AND LIMITATIONS OF THIS STUDYAn innovative protocol is developed to assess facilitated pain processing in people with cervicogenic headache.Multiple dimensions (pain processing, psychosocial lifestyle) of cervicogenic headache will be explored.No biomarkers exist to determine facilitated pain processing. The pain status can only be estimated through proxy measures such as the conditioned pain modulation and widespread hyperalgesia.If successful, the protocol can be adapted to increase clinical applicability.

## Introduction

Cervicogenic headache (CeH) is a secondary headache attributed to dysfunctions of the cervical spine.^1^ Underdiagnosed and undertreated, CeH might evolve into a chronic state, increasing the odds of absenteeism and disability.^2 3^ It is generally accepted to adopt a multidimensional approach in the management of pain.^4 5^ Interestingly though, such an approach is not recommended when managing people with CeH.^6^ Results from a Delphi-study indicated that lifestyle advice, pain education and cognitive therapy were considered not to be relevant in the management of CeH.^6^ Currently, the non-pharmacological management of CeH mainly focusses on targeting the musculoskeletal dysfunctions of the (upper) cervical spine.^6–10^ However, a meta-analysis with pooled outcome parameters showed inconsistent results of such management on headache intensity, frequency and related disability.^11^ Although non-pharmacological interventions may play an important role in managing CeH, there is currently limited scientific evidence to fully support these interventions.^11^ It has been stated previously that some therapeutic interventions are not appropriate for all people with CeH.^12^

When CeH is merely mediated by a peripheral nociceptive source (ie, musculoskeletal dysfunction of the upper cervical spine), also known as bottom-up source, this could be managed by addressing the dysfunction through manual therapy and/or specified exercises.^13^ Such management is likely to be inefficient if signs of facilitated central pain mechanisms are present. In such state, exclusively aiming at the peripheral source might act as a nociceptive stimulus maintaining facilitated central pain processing^13 14^ The pathophysiology of CeH can thus generally be explained by (a) CeH caused by an exclusive peripheral input or (b) CeH caused by peripheral input and maintained by sensitisation processes. It has been argued that characterising the involved dominant central pain mechanism might provide valuable information to increase therapy efficacy.^15^ Central pain mechanisms such as pronociceptive or antinociceptive mechanisms^16^ have, however, not extensively been examined in people with CeH. Results from a study on pain processing, showing lower extracephalic and cephalic pressure pain thresholds (PPTs) in people with CeH compared with healthy controls, might indicate a dysfunctional central pain mechanism.^17 18^

Dynamic protocols, to evoke inhibition or facilitation of pain, have been designed to evaluate endogenous pain modulation and to define a pronociceptive or antinociceptive central pain mechanism. Protocols to assess pain inhibition evaluate the conditioned pain modulation (CPM) paradigm, and pain facilitation assesses temporal summation of pain (TSP).^16^ The term CPM was created for psychophysical protocols that explore diffuse noxious inhibitory control in humans.^19^ The latter manifests as the inhibition of wide dynamic range neuronal activity by descending adrenergic pathways.^19^ CPM is measured by comparing pain induced by a test stimulus, with pain induced by the same test stimulus either during (parallel) or after (sequential) a conditioning stimulus. TSP is a nociceptive mediated process, which is considered to reflect advanced spinal synaptic facilitation in the dorsal horn (ie, behavioural correlate of wind-up).^20 21^ TSP is measured by comparing pain ratings between a single noxious stimulus and repeated equal-intensity noxious stimuli at a specific frequency. A third proxy to examine facilitated central pain mechanisms is widespread hyperalgesia.^22^

Assessing endogenous pain modulation and phenotyping^23–25^ in people with CeH within a multidimensional framework is needed in the context of therapy unresponsiveness. Despite the well-known pathophysiology of CeH, the number of non-responders to non-pharmacological non-invasive therapy amounts to 25%, and self-reported effectiveness of manual therapy is rated as 36%.^26 27^ Such therapy unresponsiveness has in other musculoskeletal disorders been related to inadequate health literacy, neural sensitivity or augmented pain processing in the central nervous system.^26 27^ Therefore, a pain modulation profile (PMP) needs to be composed. The PMP includes, besides measurements to analyse central pain mechanisms, also measurements of potential influential factors (eg, demographic, psycho social lifestyle) that can influence such mechanisms. These factors might explain some of the interindividual variability in pain perception, and, therefore, possibly also play a role in CPM.^28^ Nociceptive inputs activate complex interactions among cortical regions that are also active in cognitive, emotional and reward functions. These regions influence serotonergic and noradrenergic descending pain modulatory systems bimodally via processes between the periaqueductal grey, rostral ventromedial medulla and pontine noradrenergic nuclei, ultimately facilitating or inhibiting nociceptive input. Descending pain modulatory pathways can, therefore, be stimulated from the top-down, that is, from the brain to brainstem, by psychosocial interventions.^29–31^ Furthermore, also lifestyle factors can influence pain processing. Preliminary evidence is provided that an active lifestyle could reduce spinal nociception (ie, nociceptive flexion reflex) in healthy adults.^30^ Animal studies indicated that regular physical activity influences central cellular processes (ie, decrease neuronal excitability, alter neuroimmune signalling, increase release of endogenous opioids and serotonin in the descending pain modulatory pathways) involved in dysregulation of endogenous pain modulatory system and development of chronic pain.^32–34^ Additionally, one night of total sleep deprivation impaired descending pain modulatory pathways, facilitated spinal neuronal excitability and facilitated peripheral pain mechanisms in heathy participants.^35^

The objective of the current paper is to describe a study protocol that aims to feasibly assess the PMP as part of multidimensional profiling among people with CeH. The advantage of determining such PMP is that it offers the possibility to address the involved pain mechanism(s) within a multidimensional framework.

### Study population and setting

Participants with CeH will be screened and recruited via the neurological staff of the headache department of the AZ Vesalius hospitals (Tongeren and Bilzen, Belgium).

A detailed summary of the study population’s inclusion and exclusion criteria is provided in online supplemental table S1. A 4-week headache-diary will be distributed among the enrolled participants to collect information on the following headache characteristics: intensity, frequency, duration and medication intake. Eligible participants will need to read and sign the informed consent (collected by the principal researcher) before officially being enrolled. The experimental set-up will be at the Leuven University (Leuven, Belgium) and private practice of the principal researcher (Riemst, Belgium).

10.1136/bmjopen-2023-074743.supp1Supplementary data

### Patient and public involvement

People with CeH will be involved in the feasibility study. This study aims to gather information on arguments to participate or decline to participate, reason(s) for premature ending, appropriateness of the measurements, and barriers, adverse events or burden experienced by people with CeH. The information will be used to adapt the protocol. Feedback on possible adaptations will be provided.

### Experimental protocol

A PMP, consisting of a psychosocial lifestyle profile and pain profile, will be composed (figure 1). Three questionnaires will be used to estimate the psychosocial lifestyle profile. The pain profile will be interpreted based on three parameters (TSP, CPM, widespread hyperalgesia).

**Figure 1 F1:**
[figure not shown]
Visualisation of the composition of the PMP. CPM, conditioned pain modulation; PMP, pain modulation profile; PPT, pressure pain threshold; TSP, temporal summation of pain.

Assessment will be in a headache-free phase (=score of 0 on the Numeric Pain Rating Scale). Participants will be informed on possible adverse events and asked to abstain from vigorous physical activity, taking analgesics and caffeine-containing beverages 24 hours prior to the measurements. Prophylactic treatment(s) remain unchanged.^1^ Adverse events will be questioned after finalising the test procedures and again after 24 hours. Measurements will be performed by the principal researcher (manual therapist, >10 years clinical experience, PhD physiotherapy and rehabilitation sciences) in a chronological order (figures 2–4). The entire procedure is estimated to amount to 4 hours. An overview of the time schedule for the feasibility study is provide in online supplemental figure S1.

**Figure 2 F2:**
[figure not shown]
Visualisation of the experimental protocol regarding TSP. PP, PinPrick; TSP, temporal summation of pain; V1, ophthalmic branch trigeminal nerve.

**Figure 3 F3:**

Visualisation of the experimental protocol regarding CPM. CPA, cuff pressure algometry non-dominant calf muscle (kPa); L, left; PPT, pressure pain threshold (kPa/cm²); PPTo, pressure pain tolerance (kPa/cm²); R, right; Sub, suboccipital.

**Figure 4 F4:**

Visualisation of the experimental protocol regarding widespread pain. PPT, pressure pain threshold (kPa/cm²); L, left; R, right; Sub, suboccipital; Tib, tibialis anterior.

#### Psychosocial lifestyle profile—questionnaires

The Pittsburgh Sleep Quality Index (PSQI), Depression, Anxiety, Stress Scale (DASS-21) and Headache Impact Test (HIT-6) will be completed in a quiet room prior to the CPM, TSP and PPT measurements. Thereafter the User Experience Questionnaire will be filled in. The principal researcher will be available in case of ambiguity about the questions/statements.

#### Pain profile—TSP

Figure 2 provides a summary of the TSP protocol.

#### Pain profile—CPM

Figure 3 provides a summary of the CPM protocol that will be executed 15 min after the TSP measurements.

#### Pain profile—widespread hyperalgesia

Figure 4 provides a summary of the protocol to evaluate widespread hyperalgesia, which will be executed 15 min after the CPM measurements (online supplemental figure S2).

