##### Test stimulus: mechanical PPT and tolerance

Measurements will be performed 15 min after the TSP measurements. PPT and pressure pain tolerance (PPTo) (kPa/cm²) will be measured at the left and right suboccipital muscles using an electronic pressure algometer (Somedic AB, Stockholm, Sweden).^56^ Pressure will be perpendicularly applied directly on the suboccipital muscles, starting at 0 to maximal 1000 kPa, using a 1 cm² probe with a slope of 30 kPa/s.^17 57^ Participants will be instructed to push the stop button when the sensation of pressure first elicits pain (PPT), and when the maximum amount of pressure that could be tolerated is reached (PPTo). A trial will be performed once on the left shin (tibialis anterior muscle belly, approximately 2.5 cm lateral and 5 cm inferior to the tibial tubercle) before measuring the suboccipital muscles.^58^ Intrarater reliability of tibialis anterior PPT-measurements is good-to-excellent in people with CeH (ICC 0.82–0.92).^59^

Two repeated measurements at baseline, and two measurements parallel with the conditioning stimulus will be performed (figure 3). Averages of the extracted parameters will be used for further analysis.^60^ Test–retest reliability of PPT-measurements at the suboccipital muscles is good to excellent (ICC 0.84–0.93).^61^ Intra-rater reliability of such PPT measurements is moderate-to-good in people with CeH (ICC 0.69–0.87).^17 62^

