##### Conditioning stimulus: Cuff pressure algometry

Cuff pressure tolerance (kPa) will be measured at the non-dominant lower leg. A cuff (Nocitech, Aalborg University, Denmark) will be placed around the bare non-dominant calf muscle, mounted with 8 cm distance between its upper border and the tibial tuberosity.^63 64^ Upper and lower borders of the cuff will be marked on the skin to ensure the cuff does not move between stimulations. Pressure tolerance will be determined through the maximal amount of pressure that can be tolerated. Intensity of the cuff pressure for the conditioning stimulus will be predefined as 70% of the pressure tolerance on the non-dominant leg.^63–65^ Computer-controlled cuff algometry (LabBench CPAR+instrument) shows an excellent intrarater reliability (ICC 0.89) in healthy subjects.^66 67^ Test–retest reliability is good (ICCs 0.74–0.87) in healthy subjects.^63^

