##### Conditioned pain modulation

CPM will be assessed 3 min after determining cuff pressure tolerance. The pressure (conditioning stimulus) will be kept constant throughout the CPM protocol.^64 65^ Five seconds after inflation of the cuff, PPT and PPTo will be reassessed as described above. Participants will be informed that the conditioning stimulus will be moderately painful, but that they should focus their attention on the test stimulus. The procedure described above will be executed two times sequentially, that is, once with the PPT measurement at the left suboccipital muscles, and once with the PPT measurement at the right suboccipital muscles as test stimulus. A 15 min interval will be provided between the CPM measurements since CPM has a short lasting (<15 min) hypoalgesic effect (figure 3).^68–71^

At the moment, there is no consensus on a normal CPM effect. We propose a method described by Vaegter *et al* to categorise the CPM response as normal or impaired based on the within-subject coefficient of variation (=within-subject SD/within-subject mean) in PPT. Participants will be profiled as having an impaired CPM if the CPM response is less than or equal to the normal within-subject coefficient of variation in PPT between two repeated assessments, and as having normal CPM if the CPM response is greater than the normal variation plus the upper limit of the 95% CI.^60^

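### Tibialis anterior thresholds are read only after painful cuff inflations of one calf, and the 3-min and 15-min cuff intervals are not reconciled: a possible carryover risk that re-ordering would remove

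*Protocol article*

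**What the plan says.** All references are to the protocol article.

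- **Order.** The suboccipital and CPM block starts 15 min after temporal summation. The widespread-hyperalgesia block comes last, "which will be executed 15 min after the CPM measurements" (Pain profile—widespread hyperalgesia).
- **Cuff.** It sits on the non-dominant calf, "mounted with 8 cm distance between its upper border and the tibial tuberosity". It is first inflated to the maximum the participant can tolerate, then used at 70% of that pressure as the conditioning stimulus (Conditioning stimulus: Cuff pressure algometry). There are two CPM runs, one per suboccipital side.
- **Tibialis anterior site.** It is described for a single trial on the left shin as "approximately 2.5 cm lateral and 5 cm inferior to the tibial tubercle" (Test stimulus: mechanical PPT and tolerance). The Widespread hyperalgesia section refers back to that section for both legs, calls both sites distant and pain-free, and compares them with normative PPTs.
- **Intervals.** "CPM will be assessed 3 min after determining cuff pressure tolerance", but also: "A 15 min interval will be provided between the CPM measurements since CPM has a short lasting (<15 min) hypoalgesic effect" (both in Conditioned pain modulation).
- **After-effects.** The Feasibility part of the Discussion lists muscle soreness or sensitivity from mechanical pressure among the potential effects, expects such effects to resolve within 10 min, and gives limiting carryover as the reason for the 15-min interval after CPM.

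**The concern.** A threshold compared with normative values should be unconditioned. Here one of the two tibialis anterior sites is on the leg that has just been cuffed, close to the cuff, and the order is fixed, so every participant is exposed in the same way. Local soreness would lower the PPT and could suggest widespread hyperalgesia that is not there. Residual inhibition would raise it and could hide hyperalgesia that is. As only one leg is cuffed, any such effect could also appear as a side difference that has nothing to do with cervicogenic headache.

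The second part concerns the CPM result itself. The protocol treats conditioning at 70% of tolerance as needing 15 min before the next run, yet allows 3 min after a stronger inflation of the same cuff. Normal versus impaired CPM is decided against the within-subject variation in PPT, so carryover large relative to that variation could change a participant's category.

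**Working it through.** The protocol gives no carryover figure to reproduce. The check compares its stated intervals and distances, then adds one illustration on assumed inputs.

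**1. Exposure before the tibialis anterior PPTs.** One inflation to tolerance plus at least one per CPM run: 1 + 2 = 3 or more. It is not stated whether the tolerance test is repeated before the second run; if so, there are at least 4.

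**2. Distance on the cuffed leg.** Cuff upper border 8 cm from the tuberosity, test site about 5 cm below the tubercle: 8 − 5 = 3 cm. The site is above the cuff, not under it. This takes the two landmarks as the same point, both distances as measured down the leg, and the trial site as the one used on both legs. The dominant leg has no local cuff exposure.

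**3. Wait before the tibialis anterior PPTs, against the protocol's own figures.**

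| Requirement | Stated | Given | Difference |
|---|---|---|---|
| CPM hypoalgesia over | <15 min | 15 min | met, no shortfall |
| Recovery from local effects | 10 min | 15 min | 5 min to spare |

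**4. Wait between cuff tolerance and CPM.** 3 min, against 15 min between runs: 15 − 3 = 12 min shorter, with no reason given.

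**5. Which readings the 3 min can reach.** The text describes the suboccipital baseline, then cuff tolerance, then CPM, where "Five seconds after inflation of the cuff, PPT and PPTo will be reassessed as described above". The word used for the conditioned readings implies an earlier baseline. On that reading the first-run baseline is untouched and the 3 min bears only on the first run's conditioned values. If tolerance is not repeated, the second run's conditioned values do not follow a tolerance inflation by 3 min, so the two sides, each with its own pain profile, are conditioned after different histories. The text never states outright that the baseline comes first.

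**6. Illustration only: if the baseline did follow cuff tolerance.** Let c be the true CPM effect and r the share of a cuff effect of the same size still present at baseline. Measured CPM = (1 + c)/(1 + c·r) − 1. Neither c nor r is in the protocol. Assume c = 20% and decay of the effect by 15 min either linearly to 0, or exponentially to 5% or to 1%.

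- Linear: r at 3 min = 1 − 3/15 = 0.80; 1.20/1.160 − 1 = 3.4%
- Exponential to 5%: r = 0.05^(3/15) = 0.549; 1.20/1.110 − 1 = 8.1%
- Exponential to 1%: r = 0.01^(3/15) = 0.398; 1.20/1.080 − 1 = 11.2%

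For c from 10% to 30%, the baseline would be raised by c·r = 4 points (0.10 × 0.398) to 24 points (0.30 × 0.80) at 3 min, but by only 0 to 1.5 points (at most 0.30 × 0.05) at 15 min. The order of baseline and cuff tolerance is therefore worth stating explicitly.

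**The case against.** The strongest reply is that the protocol already provides for carryover. The tibialis anterior PPTs follow CPM by the protocol's own washout, which also exceeds its 10-min recovery figure. A reader might infer from the order and the 3-cm distance that these thresholds are contaminated. The document does not support that: it would take a local after-effect lasting beyond 15 min, and nothing in the text asserts one. Only one of the two sites is concerned, and even the sign of any effect is unknown. The pain-free label is set against the symptomatic suboccipital area, so it can fairly be read as describing the patient's headache-related pain and not the state of the leg during the session. All of this stands.

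A reader might also infer that the 3-min gap spoils the baseline. The order of the text points the other way, and the figure showing the CPM sequence is not in the copy reviewed and may settle it. Nor do the two intervals strictly contradict each other, since they govern different gaps.

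What remains is narrower. The 15 min is justified by the duration of CPM hypoalgesia, a remote inhibitory effect, whereas the question on the cuffed leg is local sensitivity, for which the protocol offers only an expectation of recovery. It also asks about adverse events again after 24 hours. The 3-min gap after the strongest inflation has no stated rationale.

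**Conclusion.** The point holds as a design weakness that is cheap to remove, not as a demonstrated bias. One of the two tibialis anterior sites is compared with normative values after at least three painful inflations about 3 cm away, on the strength of an assumed washout. The protocol's stated figures are met, so the risk is possible, confined to one leg, and of unknown direction and size. No misclassification rate can be derived: the document gives neither the spread of PPTs, nor the size of the normative sample, nor any carryover effect.

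The 3-min and 15-min intervals differ by 12 min without explanation. On the likelier reading this touches only the first run's conditioned values. The fall of a true 20% CPM effect to between 3% and 11% applies only if the baseline follows cuff tolerance and only under the decay assumptions shown.

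Feasibility is the primary outcome and the profile proportions in at least 12 participants are secondary, so neither the primary analysis nor the sample size is affected. The study is meant to refine the protocol before a larger one, which makes this the right time to settle the order.

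**What to change.** 1. Take all unconditioned PPTs, that is both tibialis anterior sites and the first-run suboccipital baseline, before the first cuff inflation. A natural place is where the left tibialis anterior trial is already done, after the break that follows temporal summation.
2. State in the text that the baseline precedes cuff tolerance, and whether cuff tolerance is determined again before the second run.
3. Reconcile the 3-min interval after cuff tolerance with the 15-min interval between CPM runs, or give the reason they differ.
4. If the present order is kept, acknowledge that one tibialis anterior site is on the cuffed leg, and report the two legs separately.

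The cost is a few minutes of re-ordering and updated figures, with no new equipment. No time saving should be claimed: the widespread-hyperalgesia block also contains an extrasegmental CPM measurement, which may still need the 15-min wait. If reconciling the intervals lengthened the shorter one to match the longer, it would add 12 min per tolerance test to a session estimated at 4 hours.
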